#### Sample size calculation

The sample size for smoking is based on the assumption that 49.2% of the population with an increased COPD risk smokes [22]. A sample size calculation by PS software [23] indicates that 446 participants will be necessary in each arm at the end of the trial to detect 20% 7-day point prevalence abstinence in the intervention group, compared to 10% in the control group [24], with a 80% power and a significance level of 0.05. Since we do not uphold an upper bound for minutes a person can be physically active, 100% of the participants will be included in the analyses for physical activity. In another study the standard deviation for the Dutch population was 26.63 [25]. Considering this, we will need 112 participants in each arm, which is feasible to obtain from the suggested sample of 446 participants in order to detect a difference of 10 minutes with 80% power and a 0.05 significance level.

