### Data collection

A self-administered web-based questionnaire will be deployed at baseline and after 6 months. All outcome measures will be collected through this questionnaire, except for the demographic characteristics in the group that is recruited online. Flycatcher members enter their demographic variables when they start their membership. These variables are updated annually.

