### Primary and secondary outcomes

One primary outcome measure per module is defined, including the 7-day point prevalence abstinence measuring smoking cessation and the short version of the IPAQ measuring the level of physical activity. Secondary outcomes are alternative smoking behaviour outcomes (i.e., current smoking behavior, 24-hour point prevalence abstinence, prolonged abstinence, continued abstinence and number of quit attempts), dyspnoea score, COPD related quality of life, stages of change and intention to change behaviour.

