### Analysis

Number (%) and mean (SD) will be computed for categorical and numerical baseline characteristics, respectively, where the differences in these characteristics are assessed between intervention and control groups by chi-square or Fisher’s exact tests for categorical variables and independent-samples t-tests for numerical variables. Data will be analysed according to the intention to treat principle. In addition, a per-protocol analysis will be conducted. For this analysis, it is required that participants complete at least one intervention component. The uncorrected and corrected effect of the intervention on the primary and secondary outcome measures at 6 months will be assessed with logistic regression for categorical outcomes and linear regression for numerical outcomes. As for correction, baseline characteristics related to the outcome at 6 months are included in the regression model to increase the precision of the intervention effect. Since randomisation is stratified by recruitment method (online or through general practices), recruitment method is also included as a covariate in these analyses. As a sensitivity analysis, the differences in baseline characteristics between the groups recruited online and through the practices are compared. If this analysis shows that the groups are comparable, the analyses will be applied to the whole dataset, otherwise the groups will be analysed separately.

Quantitative process evaluation data will be analysed using descriptive statistics, such as number (%) and mean (SD). Differences in intervention use and satisfaction with the intervention between specific subgroups, such as gender, smoking/non-smoking and age groups, will be analysed. Content analysis will be performed to analyse the qualitative process evaluation data using the constant comparative method [52]. Statistical analysis will be performed using Statistical Package for Social Sciences (SPSS) version 19.

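### Uncorrected and corrected effects are both planned with neither named as primary, and the correction covariates are apparently chosen by their relation to the 6-month outcome

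*Protocol article*

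**What the plan says.** The Analysis section states: "The uncorrected and corrected effect of the intervention on the primary and secondary outcome measures at 6 months will be assessed", by logistic regression for categorical and linear regression for numerical outcomes. The correction is defined by a rule, not a list: "baseline characteristics related to the outcome at 6 months are included in the regression model to increase the precision of the intervention effect". No threshold or selection procedure is given.

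One covariate is fixed because it stratified the randomisation: "recruitment method is also included as a covariate in these analyses". It is not clear whether this also covers the uncorrected model.

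There are two primary outcomes: "One primary outcome measure per module is defined, including the 7-day point prevalence abstinence measuring smoking cessation and the short version of the IPAQ". Neither the Primary and secondary outcomes section, nor the Analysis section, nor the Discussion says whether the uncorrected or the corrected effect is primary. The Discussion does put intention to treat before per protocol, but that is a different choice.

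Baseline values of the outcomes will be available: "A self-administered web-based questionnaire will be deployed at baseline and after 6 months". They are not named as covariates.

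**The concern.** Two features of the text combine. Each primary outcome gets two treatment effects and two p-values with no ranking, so the authors can choose between them after seeing both. And one of the two comes from a model whose content depends, on the natural reading of the rule, on associations seen in the trial's own follow-up data, so nobody can write that model down beforehand.

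At stake is the 5% error rate of each primary comparison and, for abstinence, the meaning of the estimate. An odds ratio changes when prognostic covariates enter a logistic model, even with perfectly balanced arms. The uncorrected and corrected odds ratios therefore answer different questions whenever the intervention works.

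**Working it through.** **1. The plan's own figures.** Inputs from the Sample size calculation section: 20% against 10% abstinence, 80% power, alpha 0.05, 49.2% smokers; SD 26.63 and a difference of 10 minutes for physical activity.
- Smoking, two-sided without continuity correction: n = [1.96·√(2·0.15·0.85) + 0.8416·√(0.2·0.8 + 0.1·0.9)]² / 0.10² = 199 per arm. With continuity correction: 219 smokers per arm. 219 / 0.492 = 445.1, rounded up to 446, as stated.
- Physical activity: n = 2·(1.96 + 0.8416)²·26.63² / 10² = 111.3, rounded up to 112, as stated.

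Both are unadjusted two-group calculations, so neither settles which effect is primary.

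**2. Does the selection rule alone inflate error?** Null simulation, 10,000 runs, 112 per arm. Assumed: 15 baseline variables, of which the baseline value (correlation r with the outcome) and three others (correlation 0.2 each) are truly related; selection at p<0.05; linear model.

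| r | Selected-covariate model alone | Either result significant | The two results disagree |
|---|---|---|---|
| 0.3 | 5.0% | 6.9% | 4.0% |
| 0.5 | 4.9% | 7.7% | 5.7% |
| 0.7 | 5.1% | 9.0% | 7.3% |

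The corrected model alone holds 5%. The excess appears only when either result may be claimed.

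**3. Closed-form check of the third column.** With no effect, the two test statistics have correlation of about √(1 − R²), where R² is the share of outcome variance that the covariates explain; here R² = r² + 3·0.2². That gives R² = 0.21, 0.37, 0.61 and correlations 0.889, 0.794, 0.624. The bivariate normal probability that at least one exceeds 1.96 in absolute value is then 7.1%, 7.8% and 8.7%, in line with the table. The size is driven mainly by R².

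Other null runs agree: 7.0% with 219 per arm, 15 candidates and 5 prognostic (3,000 runs; corrected model alone 4.8%), and 6.6% to 7.4% at the planned trial size (corrected model alone 4.6% to 5.3%).

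**4. Would baseline physical activity be left out?** All participants enter this analysis, 2 × 446 = 892. By Fisher's z, the chance of selection at p<0.05 for r = 0.3 is Φ(atanh(0.3)·√(n − 3) − 1.96). For n = 892 this is Φ(9.23 − 1.96), above 99.99%; for n = 224 it is Φ(4.60 − 1.96) = 99.6%. Adjustment cuts residual variance by r², which is 9%, 25% and 49% at r = 0.3, 0.5 and 0.7. Since the rule would almost always capture that gain, it is not a loss under the plan.

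**5. Abstinence.**
- Expected quitters among 2 × 219 smokers: 219·0.10 + 219·0.20 = 65.7, about 66 under the design assumption; 2·219·0.10 = 43.8, about 44 if both arms are at 10%.
- The Demographic characteristics section alone lists at least 16 variables, several with multiple categories. With 15 candidates there would be 66/15 = 4.4 or 44/15 = 2.9 quitters per candidate, a thin basis for data-driven selection.
- The design assumption corresponds to an uncorrected odds ratio of (0.20/0.80) / (0.10/0.90) = 2.25. An odds ratio conditional on prognostic covariates would lie further from 1 for the same intervention. With no effect both equal 1, so this concerns interpretation and not false positives.

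**The case against.** The strongest reply has four parts.

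- **Outcome-driven selection is harmless here.** A reader might infer that picking covariates by their relation to the outcome inflates the error rate. It does not: inclusion depends on relation to the outcome, not on the treatment estimate, and the corrected model alone stays at about 5%. This stands.
- **Baseline activity would be selected anyway.** A reader might infer that the plan forfeits the 9% to 49% variance reduction. It does not, because the stated rule picks up any strong predictor. This also stands. For abstinence among baseline smokers, the population implied by "49.2% of the population with an increased COPD risk smokes", the baseline value is nearly constant and the issue does not arise.
- **Nothing says that success on either result suffices.** True. The 6.6% to 9% is what the text permits, not what it prescribes, and reporting both results side by side is transparent. But without a ranking, nothing tells the reader which result counts when they disagree.
- **Covariate lists belong in an analysis plan, and the rule could mean factors known from earlier work.** A missing list alone would be no finding. Here, however, the article states a rule and commits to two unranked effects. A later list would replace that rule, not fill it in. If prior knowledge is meant, the wording does not say so.

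**Conclusion.** The point holds in a limited form. The plan gives two unranked effects per primary outcome and, on the natural reading, an adjustment model that cannot be known before the results. The cost is about 7% false positives per primary outcome instead of 5% if either result may be claimed. The range of about 6.6% to 9% rests on assumptions that the article does not supply: 15 to 30 candidates, selection at p<0.05, and a baseline correlation of 0.3 to 0.7. For abstinence there are also two different odds-ratio estimands when there is an effect, and an open model resting on about 44 to 66 quitters. The documents support neither inflation from the selection itself nor a material loss of precision for physical activity. Nor do they show any intention to claim the better result; the defect is that the text leaves this open.

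**What to change.** Replace the outcome-driven rule with covariates fixed before any follow-up data are seen, and make that corrected model the single primary analysis for each primary outcome:

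- **Physical activity:** recruitment method plus baseline IPAQ minutes.
- **7-day abstinence:** recruitment method plus a short fixed list of predictors already in the baseline questionnaire, chosen by the investigators. Candidates include the nicotine dependence score, intention to quit or stage of change, and COPD diagnosis. The list should be short because quitters will be few.
- **Continuous secondary outcomes:** recruitment method plus the outcome's own baseline value.

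Label the uncorrected effect as supportive and say whether it includes recruitment method. For abstinence, state that the primary odds ratio is conditional on the listed covariates.

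The cost is a few sentences. The variables are already collected, and the stated 446 and 112 per arm do not change. What is given up is the freedom to choose the model or the headline result after the data are in.

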#### Randomisation

Participants will be randomly allocated to intervention and control groups after filling out the baseline questionnaire. Randomization will be stratified by method of recruitment (online or through general practice) and participants are randomised within each stratum using a permuted block design with a random block size varying from 4 to 20. This approach helps us achieve balanced and evenly distributed samples in both groups following different recruitment strategies. A researcher who is not directly involved in other aspects of the study will perform the randomisation using PROC PLAN in Statistical Analysis System v9.1 software (SAS Institute, Cary, NC). Figure 1 shows an overview of the recruitment and randomisation process.

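### A baseline comparison of the two recruitment routes decides whether the trial is analysed whole or in two parts; this is the wrong trigger, and a split costs smoking power without any gain in validity

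*Protocol article*

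**What the plan says.** All references are to the protocol article.

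- **Randomisation:** "Randomization will be stratified by method of recruitment (online or through general practice". Permuted blocks are used within each stratum.
- **Analysis:** logistic and linear regression estimate the intervention effect on the primary and secondary outcomes at 6 months. Because of the stratification, "recruitment method is also included as a covariate in these analyses".
- **Analysis, next step:** under the label of a sensitivity analysis, baseline characteristics are compared between online and practice recruits. Then: "If this analysis shows that the groups are comparable, the analyses will be applied to the whole dataset, otherwise the groups will be analysed separately".
- **Sample size calculation:** "446 participants will be necessary in each arm at the end of the trial". This is a single figure for the whole trial, with no allowance for analysing the routes apart.
- **Discussion:** recruiting partly online is defended as a way to make adequate power more likely, after recruitment through practice nurses in the pilot fell short.

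**The concern.** Despite its label, the step is not a supplementary check. Its second branch replaces the analysis of the whole dataset with two separate ones, so it governs the main result.

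The trigger does not match the decision. Whether the routes differ at baseline is a question about who was recruited. Whether they should be analysed apart is a question about whether the intervention effect differs between them. The first does not answer the second, and the stratified randomisation and route covariate already deal with prognostic differences between routes.

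If the split is taken, the outcome that sets the sample size loses its planned power. Each primary hypothesis then has two answers, and the article does not say how they are to be combined if they disagree. The route covariate, constant within each part, drops out. The split also undoes the stated reason for combining the two sources.

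**Working it through.** **1. Does a baseline difference between routes threaten the pooled comparison?** Arms are allocated at random within each route, so the expected mix of routes is the same in both arms. A characteristic that differs between routes is therefore not associated with arm by design. If it is prognostic, the route covariate absorbs the between-route part. Pooling is valid whether or not the routes are alike. A different effect by route would appear as an arm-by-route interaction, which a comparison of baseline characteristics does not examine.

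**2. Reproducing the plan's sample sizes.** Inputs from the Sample size calculation section:

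- Smoking: "to detect 20% 7-day point prevalence abstinence in the intervention group, compared to 10% in the control group", "with a 80% power and a significance level of 0.05" (taken as two-sided), and "49.2% of the population with an increased COPD risk smokes".
- Physical activity: "In another study the standard deviation for the Dutch population was 26.63", with a difference of 10 minutes at the same power and level.

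Smoking, with d = 0.10 and mean proportion 0.15:

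- Uncorrected n = [1.96·√(2·0.15·0.85) + 0.8416·√(0.2·0.8 + 0.1·0.9)]² / 0.10² = (0.990 + 0.421)² / 0.01, rounded up to 199 smokers per arm.
- Continuity-corrected n = (n/4)·[1 + √(1 + 4/(n·d))]², rounded up to 219 smokers per arm.
- 219 / 0.492 = 445.1, rounded up to **446**, the stated figure. Without the correction, 199 / 0.492 = 404.5, which does not match. The plan's method is therefore the continuity-corrected one.

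Physical activity: n = 2·(1.96 + 0.8416)²·26.63² / 10² = 111.3, rounded up to **112** per arm, also as stated.

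**3. Power after a split.** Assumptions: 446 per arm in total, the same 49.2% of smokers and the same 20% versus 10% in both routes, and route shares that are mine because the article gives none.

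- Smokers per arm in a route: n = 446 × 0.492 × share = 219.4 × share.
- Inverting the continuity correction gives an effective size m = (n − 1/d)² / n = (n − 10)² / n.
- Smoking power = Φ{[0.10·√m − 1.96·√0.255] / √0.25}. The uncorrected version uses n in place of m.
- Physical activity power = Φ{10 / [26.63·√(2/N)] − 1.96}, with N = 446 × share.

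Worked case at a 50% share: n = 109.7 and m = 99.7² / 109.7 = 90.6. Power = Φ[(0.952 − 0.990) / 0.5] = Φ(−0.076) = 47%.

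| Route's share | N per arm | Smokers per arm | Smoking power, corrected | Smoking power, uncorrected | Physical activity power |
|---|---|---|---|---|---|
| 100% (pooled) | 446 | 219.4 | 80% | 84% | >99% |
| 90% | 401 | 197.5 | 75% | 80% | >99% |
| 80% | 357 | 175.5 | 70% | 75% | >99% |
| 70% | 312 | 153.6 | 63% | 69% | >99% |
| 50% | 223 | 109.7 | 47% | 55% | 98% |
| 30% | 134 | 65.8 | 27% | 36% | 87% |
| 20% | 89 | 43.9 | 17% | 26% | 71% |
| 10% | 45 | 21.9 | 7% | 15% | 43% |

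Physical activity keeps 80% in a route with at least 112 per arm, that is, a share of at least 112 / 446 = 25%.

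**4. What larger recruitment would have to reach.** A route analysed alone has the planned smoking power only if it supplies 446 per arm itself. For both routes to do so, the total must be at least 2 × 446 = 892 per arm at 50/50, or 446 / 0.20 = 2,230 per arm at 80/20.

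**The case against.** Several points on the other side stand and limit the finding.

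- **No bias from the split.** Each route-specific analysis is a randomised comparison within its stratum. The loss is of precision and of a single answer.
- **No outcome data are used.** A reader might infer that the analysis is chosen after seeing results. The text does not support that: the branch is written in advance and turns on baseline characteristics only.
- **446 is a requirement, not a ceiling.** The Recruitment section invites all active panel members aged 40 to 70 and gives no cap or panel size. The online route alone might reach 446 per arm. The power figures hold at a total of 446 and soften above it.
- **One primary outcome is largely unaffected.** A reader might infer that both primary outcomes lose their planned power. Physical activity does so only in a route with less than about a quarter of the sample.
- **The chance of a split cannot be quantified.** It is tempting to say that the routes will almost certainly differ, or that chance alone will often trigger the rule. The article names no test, threshold or variable list for this comparison, and both routes share the age limits and the risk questionnaire. A criterion may also stand in an analysis plan not shown, so its absence carries no weight here.
- **Error inflation across route-specific tests is not established.** It would need a rule that any one positive test counts as success, and none is stated.

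One might add that the preceding sentence already specifies the pooled, route-adjusted model and that the step is called a sensitivity analysis. That does not remove the problem, because the second branch takes the pooled analysis away.

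**Conclusion.** The concern holds in this form: a baseline comparison between routes is the wrong trigger for abandoning the pooled analysis, and the split buys no validity because the design and the model already account for route. This conclusion needs no assumption beyond the article's own Randomisation and Analysis sections.

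The size of the harm does rest on assumptions. At 446 per arm in total, with equal smoking prevalence and effect in both routes, no route keeps the planned smoking power on the plan's continuity-corrected method at any split tried. The best case is 75% in the larger route at 90/10, with 7% in the smaller. Without the correction, that larger route comes back to about 80%, and no other route does. For physical activity the loss is confined to a small route.

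The documents do not support a stronger reading, such as a biased estimate, outcome-driven choice of analysis, or a quantified inflation of false-positive error. What remains is an avoidable loss of precision on the outcome that sets the sample size, and two results per primary hypothesis with no stated way to reconcile them.

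**What to change.** Delete the conditional sentence and replace it with text to this effect: the primary analysis always includes all randomised participants from both recruitment routes (for abstinence, the smokers among them, as the sample-size arithmetic implies), with recruitment method as a covariate, whatever the baseline comparison of routes shows.

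Then:

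- keep the baseline comparison of online and practice recruits as description only;
- add an arm-by-recruitment-method interaction for each primary outcome, labelled exploratory, with route-specific estimates and confidence intervals.

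The cost is an edit to one sentence and one short addition in the Analysis section. Sample size, randomisation and data collection do not change. Because the rule acts on baseline data, the edit should be made before the routes are compared.

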## Discussion

This paper presents the design of a randomised controlled trial, testing the effectiveness of a computer-tailored intervention on the self-management of people with or at risk for COPD. To our knowledge, only limited research has been conducted to evaluate self-management interventions for COPD patients [3] and none of these studies used computer-tailored technology. The results of this study explore the potential benefit of using computer-tailored technology to improve self-management related health behaviours of people at risk for COPD, in addition to those with COPD.

Individuals at risk for COPD are less likely to be offered a self-management intervention by a health care provider, but they can be reached relatively easily through the internet and health behaviour change can be promoted. We also expect that including people at risk for COPD and recruiting some of the participants online increases the likelihood of assuring adequate power.

The choice for a hybrid sample of participants recruited by two methods (online panel and general practice) was made after considering the results of the pilot study (unpublished observations). In the pilot study participants were recruited by a primary care practice nurse during a yearly consultation for routine monitoring of their chronic condition. This recruitment strategy resulted in an insufficient number of participants. Not all eligible patients were invited by the nurses and many patients declined participation. We concluded that it is not feasible to recruit 446 participants per arm using this approach. Therefore, we choose to recruit participants from an online panel and through general practices by sending an invitation letter to every eligible patient.

A possible threat to this study is that large numbers of participants might not use or discontinue to use the intervention, which is common in e-Health interventions [53]. If a large percentage of participants opt not to use the intervention, an intention to treat analysis could underestimate the intervention effect [54]. For this reason we will conduct a per-protocol analysis following an intention to treat analysis.

One of the strengths of this study is that we conduct a process evaluation to assess the implementation of the study protocol. A process evaluation enables researchers to explain study outcomes and helps understand why an intervention was effective or not [51]. As another advantage, recommendations can be formulated for further research in order to study specific aspects of the technology implementation.

